### Intervention description {11a}

Stretching exercises and tDCS are performed by one expert and trained physiotherapist with 8 years of experience in these fields. The interventions take a total of 10 min, and individuals in the slump posture group will receive exercises or tDCS, before typing in one of the three sessions of the study.

#### Stretching exercise

Exercise is a recommended intervention for computer users [29]. It was reported that stretching exercises had become more accepted in workplaces [30]. Therefore, three sets of nine stretching exercises will be used to improve the flexibility of muscles in the neck, shoulder, upper limbs, and back. These exercises are selected based on the review of Lee et.al, who assessed different types of exercises for VDT (Video Display Terminal) operators and office workers [31]. It takes a total of 10 min to perform the exercises, and individuals in the slump posture group will do these exercises before typing in one of the three sessions of the study. They are taught to stretch the muscles slowly and constantly until they feel mild discomfort, and then hold this position for 15 s. A break of 60 s is considered between sets.

#### tDCS

To provide transcranial direct current stimulation, an Oasis Pro DC stimulator (Mind Alive company, Canada) will be used. According to previous studies, stimulation of the left dorsolateral prefrontal cortex (DLPFC) makes improvements in cognitive functions such as decision-making, attention, and working memory [32–38]. Therefore, the anode is placed over F3 according to the 10–20 system, and the cathode is placed on the supraorbital region of the opposite side. A current of 2 mA is applied through two 3 cm × 5 cm conductive rubber electrodes inside a sponge soaked with physiologic saline [39]. The stimulation increases during a 30 s ramp up to 2 mA, it is stabilized for 10 min, then reduces to zero over the last 30 s. At the time of receiving current by participants, continuous monitoring of the output current will be done.

### Criteria for discontinuing or modifying allocated interventions {11b}

If subjects report seven or higher level of itching, tingling, and heat based on 10-point Likert scale, tDCS will be stopped.

### Strategies to improve adherence to interventions {11c}

Stretching exercises and tDCS will be performed in two separate sessions under the supervision of an experienced physiotherapist.

### Relevant concomitant care permitted or prohibited during the trial {11d}

The subjects will be told that all relevant concomitant care and treatments such as postural corrective exercises, are prohibited during participation in this study**.**

### Provisions for post-trial care {30}

No mental or physical damage is anticipated due to evaluations or interventions. However, if people are harmed during this study because of evaluations or interventions, this will be reported to the Tehran University of Medical Sciences ethics committee and the research team of this study will take responsibility for free treatment.

### Outcomes {12}

#### Task performance

Task performance will be obtained by typing speed (i.e., characters per minute) and typing errors (i.e., errors per minute), which will be calculated by the assessor at the end of the tests.

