## Introduction

### Background and rationale {6a}

The employees are used to spending long periods of time in front of a computer with a dorsiflexed posture [1], in fact requiring high concentration and focus while working with a computer causes them not to pay attention to the body position. This lack of awareness of the body posture is one of the important reasons for poor posture among office workers [2].

Poor posture can change physiological, structural, physical, and functional aspects; furthermore, it can affect learning and attention [3]. For instance, slump posture decreases the rate of speaking compared to sitting upright [4] and slouched posture makes it difficult to do a math test [5]. According to Lee et al.’s study, forward head posture negatively influences the state of rest and concentration of the brain, as measured by a neuro-feedback system [6]. Based on these studies, it can be expected that poor posture causes or aggravates mental fatigue.

Mental fatigue is defined by feeling sleepy and drowsy while needing to concentrate [7] and has indicators such as feeling tired, a decrease in energy [8], mood changes [9], a decrease in performance, a decrease in accuracy and an increase in reaction time [9, 10], as well as changes in brain activity [7]. Mental fatigue has a negative impact not only on task performance in different environments, such as school [11] and workplace [12], but also on the safety of people [13]. For example; the risk of fatigue-related accidents increases, when employees get stuck in traffic after a long work day [14]. In some cases, such as those of industry workers, surgeons, drivers, and pilots, mental fatigue can lead to many hazards that cause both economic and human losses [12, 15]. Considering the high prevalence of mental fatigue in everyday modern life, it is necessary to search for efficient interventions to improve task productivity and occupational health. To date, the number of studies on tackling mental fatigue is fairly limited [16].

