### Objectives {7}

The main objective of this study is to compare the mental fatigue through EEG during a prolonged typing task (i.e., 60 min) between subjects with slump and normal postures and to determine whether using tDCS or stretching exercises in the slump posture group, can deal with mental fatigue and minimize the difference in terms of mental fatigue between slump and normal posture groups.

Secondary objectives of the study include the following:To compare the kinematic parameters (i.e., entropy of neck motion and cervical angle), task performance (i.e., typing speed and errors), musculoskeletal discomfort, and visual analog fatigue scale between subjects with slump and normal postures.To compare the kinematic parameters (i.e., entropy of neck motion and cervical angle), task performance (i.e., typing speed and errors), musculoskeletal discomfort, and visual analog fatigue scale between slump posture following performing stretching exercise and normal posture.To compare the kinematic parameters (i.e., entropy of neck motion and cervical angle), task performance (i.e., typing speed and errors), musculoskeletal discomfort, and visual analog fatigue scale between slump posture following tDCS and normal postureTo compare the kinematic parameters (i.e., entropy of neck motion and cervical angle), task performance (i.e., typing speed and errors), musculoskeletal discomfort, and visual analog fatigue scale between 3 conditions of stretching exercise, tDCS, and no intervention in slump posture group.

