#### Task

Previous research showed that working with a computer for a period of 45 to 60 min had reduced the performance to its minimum level [26]. So, in this study, 60 min are considered for typing, and spell-check of the word program will be turned off for all conditions. Three different Persian texts from a single book are selected for the study. The same text will be used for individuals with normal and slump posture (i.e., no intervention). But for the intervention sessions, the text will be changed to prevent the learning effect.

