## Statistical methods

### Statistical methods for primary and secondary outcomes {20a}

Data analysis will be performed using SPSS, version 22 (IBM, NY, USA). Baseline characteristics such as age, weight, height, BMI, years of computer use, and daily computer usage will be summarized with standard descriptive statistics. Depended variables will be described with means and standard deviations. The normality of distribution will be checked by Kolmogorov–Smirnov.

Multivariate ANOVA (MANOVA) will be used to compare the variables between correct and slump posture groups.

Statistical analysis of the outcomes of 3 conditions in the slump posture group will be conducted using repeated measures ANOVA and LSD (least significant difference) post hoc test. The significance level of tests will be considered at 0.05. Mean difference and standardized mean difference and their 95% confidence intervals (Cohen’s D) will be calculated as effect sizes.

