### Methods for additional analyses (e.g., subgroup analyses) {20b}

There will be no additional analyses for the present study.

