## Discussion

To the best of our knowledge, this is the first study to investigate the impact of poor posture on mental fatigue.

Different techniques have been employed to measure mental fatigue. These methods are classified subjectively, behaviorally, and physiologically [43].

Subjectively, decreased energy [8], alertness [44], or motivation [45] with an increase in feelings of tiredness [8] are the characters of mental fatigue. In this method, standard questionnaires such as F-VAS have been used [43]. Behaviorally, performance deterioration including decreased in accuracy and slower responses, occurs following mental fatigue [9, 10, 46]. Effects of mental fatigue on performance have been studied since the beginning of the nineteenth century; Different theories about cognitive mechanisms have been proposed in this issue. According to these studies, people begin to experience mentally tired and their performance deteriorates when the costs of doing a task overtake the benefits of finishing that task [13]. Performance can be measured in different ways; For employees who are prone to mental fatigue, computer typing provides information about the level of mental fatigue without interfering with regular work activities [13, 47]. Physiologically, mental fatigue is detected by tracking alternations in the neural activity of the cortex [9, 48–50]. EEG spectral band change has been considered a reliable biomarker to detect mental fatigue. Increased slow-band EEG activity (i.e., 4–13 Hz), is associated with decreased mental activity [7].

Recent studies have revealed that mental fatigue has a negative effect on neuromuscular function including strength, muscle activity, and joint steadiness [51]. According to Marcora et al. (2009), during the condition of mental fatigue, people experience greater discomfort, decreased muscle endurance, and a higher perception of effort [46]. These changes in neuromuscular function may lead to loading of the musculoskeletal system and changes in kinematic parameters.

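### Typing errors are scored per minute, which mixes accuracy with speed and can hide or reverse an accuracy loss in the slower group or condition

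*Protocol article*

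**What the plan says.** The Task performance paragraph under Outcomes {12} names two components. The first is speed: "Task performance will be obtained by typing speed (i.e., characters per minute". The second is "typing errors (i.e., errors per minute". Both are calculated by the assessor at the end of the tests. The Task paragraph fixes the duration and not the amount of text: "60 min are considered for typing, and spell-check of the word program will be turned off for all conditions".

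Objectives {7} places "task performance (i.e., typing speed and errors" among the secondary objectives. It is compared between slump and normal posture, between slump posture after each intervention and normal posture, and among the three conditions within the slump group.

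The article expects fatigue to affect both aspects of performance. Background and rationale {6a} lists among its indicators "a decrease in performance, a decrease in accuracy and an increase in reaction time". The Discussion says that "performance deterioration including decreased in accuracy and slower responses, occurs following mental fatigue".

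For the analysis, section {20a} states "Multivariate ANOVA (MANOVA) will be used to compare the variables between correct and slump posture groups", and repeated measures ANOVA with LSD post hoc tests for the three conditions. No adjustment of errors for speed is stated. Section {20b} adds: "There will be no additional analyses for the present study".

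**The concern.** With a fixed typing time, a slower typist produces fewer characters and so has fewer opportunities to make an error. A count of errors divided by time therefore depends on how fast a person types as well as on how carefully. The article's own account of fatigue has people slowing and becoming less accurate together, and these two changes push errors per minute in opposite directions.

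Both parts of the study are exposed. In the posture comparison, a difference in typing speed between groups would appear as a difference in errors even if both groups were equally accurate. In the crossover, an intervention that preserves speed, which is a hoped-for benefit, would show more errors per minute at unchanged accuracy. What is at stake is the direction and size of one of the two task-performance results.

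**Working it through.** The article states no figure for this outcome, so there is nothing to reproduce. The check is an identity followed by illustrative values.

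**Inputs from the article:** errors per minute and characters per minute (Task performance); fixed 60 min of typing (Task).

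**Assumed inputs:** relative slowing s and relative rise in errors per character e. Both are contrasts between the groups or conditions being compared, because slowing that is equal on both sides does not distort the comparison. The starting values of 150 characters/min and 2% errors are also assumed, but the percentage changes do not depend on them.

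**Step 1, identity.** Errors/min = (characters/min) × (errors/character).

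**Step 2, relative difference.** If one side is slower by s and has errors per character higher by e, its errors/min differs by (1−s)(1+e) − 1. For any s > 0 this is smaller than e, the true difference in errors per character. The shortfall is e − [(1−s)(1+e) − 1] = s(1+e).

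**Step 3, break-even.** The expression in step 2 is negative when e < s/(1−s):

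| Slowing s | Break-even s/(1−s) | Difference in errors/min if accuracy is equal (e = 0) |
|---|---|---|
| 5% | 5.3% | −5% |
| 10% | 11.1% | −10% |
| 15% | 17.6% | −15% |
| 20% | 25.0% | −20% |
| 30% | 42.9% | −30% |

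**Step 4, worked case.** Take s = 15% and e = 10%.
- Reference side: 150 × 0.02 = 3.0 errors/min.
- Slower side: 150 × 0.85 = 127.5 characters/min and 2% × 1.10 = 2.2% errors, so 127.5 × 0.022 = 2.805 errors/min.
- Errors/min: 2.805/3.0 − 1 = −6.5%, an apparent improvement.
- Errors per 100 characters: 2.0 to 2.2, or +10%, the actual deterioration.

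**Step 5, the direction is not always reversed.** At s = 20%, errors/min differs by −12% for e = 10%, −4% for e = 20% and +4% for e = 30%. In the last case the direction is right, but a 30% loss is shown as 4%.

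**Step 6, does the planned analysis undo this?** A MANOVA with speed and errors/min as separate variables does not test their ratio, and the mean differences and Cohen's d in section {20a} for the error variable would stay on the per-minute scale. The repeated measures ANOVA, as described, states no adjustment for speed either.

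**The case against.** The strongest reply has four parts.

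- **The outcome is not called accuracy.** The article calls it typing errors. Errors per unit of working time, beside output per unit of working time, is a coherent description of productivity, which is one of the study's stated interests. This stands in part: errors per minute is a legitimate quantity to report. But the article names loss of accuracy as a behavioural sign of fatigue, and typing errors are the only listed outcome that could show it.
- **Errors are always paired with speed.** A group that slows shows its deficit on speed, and an intervention that preserves speed is credited there. This also stands, and it limits the harm to readers who take the error result alone. No rule for reading the two together is stated.
- **No information is lost.** Individual ratios can be computed from the collected data, and the datasets are offered on reasonable request. That is correct for anyone holding the data. A reader of published means and standard deviations cannot recover the mean of the individual ratios, its confidence interval or a test, and a ratio chosen after the results are seen would be post hoc.
- **The sizes are hypothetical.** This stands in full. The article gives no typing speed, error rate or expected difference in slowing.

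A reader might go further and infer that errors per minute falls whenever typing slows, or that it carries no information on accuracy, so that fatigue will appear as better accuracy in this trial. The documents do not support that. The measure mixes accuracy with speed and does not exclude accuracy. Reversal needs the relative slowing between the compared sides to outweigh the accuracy loss, and nothing in the article shows that it will.

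**Conclusion.** The point holds as a defect in how one component of a secondary outcome is defined. Errors per minute mixes per-character accuracy with speed. It understates the accuracy loss of whichever side types more slowly, and shows a false improvement when that side's errors per character are higher by less than s/(1−s).

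The identity and the break-even formula rest on no assumption beyond both rates being taken over the same window. The slowing and error percentages put into them are assumptions. Whether a reversal would occur in this trial, and how large it would be, cannot be determined from the article. The EEG primary outcome, sample size, randomisation and data collection are not affected. The change is worth making because it is specific and nearly free, and because the article's own account of fatigue describes slowing and accuracy loss together.

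**What to change.** In the Task performance definition, set the error outcome to be analysed as errors per 100 characters typed, with errors and characters counted over the same window and the ratio computed for each participant in each session. Keep characters per minute as the speed outcome. Errors per minute may still be reported, with a sentence saying that it is to be interpreted jointly with speed and is not evidence of accuracy on its own.

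The cost is one or two lines of text. Both rates are already to be calculated for each test, and over a common window 100 × (errors per minute) / (characters per minute) gives the new measure, so no extra data collection is needed. The change should be fixed before the typing results are examined by group or condition, or else reported as made afterwards.

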#### Subjective assessment

Musculoskeletal discomfort will be measured through a visual analog discomfort scale and a body-part diagram divided into 15 regions (i.e., neck, upper back, lower back, left and right sides of the shoulder, forearm, wrist, thigh, knee, and lower leg). Participants will be asked to mark their musculoskeletal discomfort based on a 10-cm horizontal line (from 0 to 10 cm which indicates “no discomfort” and “extreme discomfort,” respectively) and mark the location of pain on the body-part diagram [40].

Mental fatigue will be measured using a visual analog fatigue scale. This scale is a horizontal line ranging from 0 to 10 cm. Participants will be asked to mark the line based on the intensity of their mental fatigue (from 0 cm showing ‘no mental fatigue’ to 10 cm indicating ‘maximal mental fatigue’) [41].

#### Kinematic parameters

Kinematic properties including the non-linear dynamical features of neck motion and cervical angle changes will be measured. For this, markers will be placed on the tragus, spinous process of C7, and corner of the eye. A SAMSUNG (A50, South Korea) camera (30 frames per second) will be placed at a distance of 2.18 m from the participant and a height of 1.25 m [42]. In the first and last three minutes of typing, a recording will be taken. Then the recording will be imported to Kinovea software version 0.8.15.

Mean and standard deviations of CVAs will be used to assess the cervical angle changes, and Sample Entropy will be calculated for neck motion Entropy. Entropy Analysis will be calculated in Excel software using SEN = -ΣPi ln Pi formula for each marker, where Pi is the spectral amplitudes of path bin i, Σ Pi = 1, and ln = denotes the natural logarithm.

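### Neck-motion entropy is named Sample Entropy, but the formula given is spectral (Shannon) entropy, which cannot identify non-linear dynamics

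*Protocol article*

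**What the plan says.** Three statements stand together in the protocol article under Outcomes {12}, Kinematic parameters.

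- The construct: the kinematic measures are to include "the non-linear dynamical features of neck motion".
- The measure: "Sample Entropy will be calculated for neck motion Entropy".
- The calculation: a spreadsheet computation, separately for each marker, of minus the sum of Pi ln Pi. The terms are scaled to sum to 1, and their definition reads "where Pi is the spectral amplitudes of path bin i".

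Objectives {7} carries the outcome into each of the four secondary objectives as "entropy of neck motion and cervical angle": slump against normal posture, slump after stretching against normal, slump after tDCS against normal, and the three conditions within the slump group. No other section says which of the two entropies is meant.

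**The concern.** The name and the formula belong to different quantities. Sample Entropy is built from template matching: it asks how often stretches of the series that agree over m points still agree at the next point, within a tolerance r. The printed formula has no templates, no m and no r. It measures how evenly amplitude is spread over frequency.

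Both sentences cannot be followed with one calculation. If the formula is followed, a spectral measure is reported under the Sample Entropy label, and a claim about non-linear dynamics rests on a statistic that cannot support it. If the name is followed, the printed formula is set aside. Leaving this open lets the measure be chosen after the data are in hand.

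**Working it through.** The plan states no figure to reproduce here, so the check compares definitions and then computes both quantities on synthetic series.

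**Inputs**
- Frame rate: 30 per second; recording window: 3 min (Kinematic parameters). Series length: 30 × 180 = 5,400 points.
- m and r are not given. Assumed: m = 2, r = 0.2 SD.

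**Formulas**
- As printed: H = −Σ Pi ln Pi, with Pi the Fourier amplitudes scaled to sum to 1. With 2,700 bins the maximum is ln 2,700 = 7.90.
- Sample Entropy: −ln(A/B), with A and B the numbers of template matches of length m + 1 and m within tolerance r.

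**Step 1: same spectrum, different dynamics.** A phase-randomised copy keeps the amplitude spectrum and destroys non-linear structure.

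| Series | H: series / copy | Sample Entropy: series / copy |
|---|---|---|
| Logistic map, parameter 4 | 7.758 / 7.758 | 0.64 / 2.17 |
| Logistic map, parameter 3.99 | 7.7438 / 7.7438 | 0.598 / 2.155 |
| Hénon map | 7.6836 / 7.6836 | 0.458 / 2.107 |
| AR(1), coefficient 0.95 | 7.1034 / 7.1034 | 1.073 / 1.085 |

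The first row gives 2.17 / 0.64 = 3.4, the second 2.155 / 0.598 = 3.6, the third 2.107 / 0.458 = 4.6. The linear series gives 1.085 / 1.073 = 1.01. Equal H in every row is guaranteed by how the copy is made. For the Hénon series, Sample Entropy stays between 0.448 and 0.522 over m = 2 to 3 and r = 0.1 to 0.2 SD, so that contrast does not hang on the assumed settings.

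**Step 2: ranking across series.** The formula puts the logistic map (parameter 3.99) above the AR(1) series (7.74 against 7.10); Sample Entropy puts it below (0.598 against 1.073). The two can therefore order signals in opposite directions.

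**Step 3: linear series only.**

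| Series | H | Sample Entropy |
|---|---|---|
| White noise | 7.76 | 2.19 |
| AR(1) 0.5 | 7.69 | 2.07 |
| AR(1) 0.8 | 7.49 | 1.69 |
| AR(1) 0.95 | 7.08 | 1.05 |
| AR(1) 0.99 | 6.66 | 0.54 |

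Here the two agree on order. Small differences from Step 1 for AR(1) 0.95 reflect different random draws.

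**Step 4: does the formula respond to time order?** Shuffling an AR(1) 0.95 series moves H from 7.10 to 7.77. It does, because the amplitude spectrum determines the autocorrelation. What it loses is phase.

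**The case against.** The strongest reply is that the plan does state an operational calculation, per marker and the same for every group and condition. Comparisons within the trial therefore remain valid for what the formula measures, and spectral entropy is a legitimate description of how broad the movement spectrum is. That stands: the defect is in the label and the claim attached to it, not in the comparability of groups.

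It can also be said that the contrast in Step 1 is built in, since the copies share the spectrum by design and the series are chaotic maps that nothing in the protocol likens to neck motion during typing. That stands too. A reader might infer that the planned measure would miss a threefold difference in this trial; the AR(1) row and Step 3 show why that does not follow.

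A reader might further infer that the formula ignores the order of the observations. With Pi defined as spectral amplitudes it does not, as Step 4 shows. The reference to a path bin is loosely worded. Were it read as a histogram of positions, time order would be lost, but the result would still be a Shannon entropy and not Sample Entropy.

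Finally, the absence of m and r is no fault in itself, since such settings may be left to an analysis plan or fuller protocol. The objection is to a formula that is stated and belongs to another quantity; condensing for a journal does not explain that.

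**Conclusion.** The point holds as an inconsistency that is wrong as written. The protocol names Sample Entropy and claims non-linear features, yet defines the Shannon entropy of the amplitude spectrum, which cannot separate non-linear from linear dynamics with the same spectrum. This follows from the definitions and needs no assumption about the data.

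The numerical size does rest on assumptions. About 0.64 against 2.17, with identical values on the formula, is a worst case on synthetic data with m = 2 and r = 0.2 SD. The documents give no basis for estimating the effect on neck recordings, and it could be small if the motion is close to linear. The consequence is confined to one secondary kinematic variable, though one named in all four secondary objectives. The EEG primary outcome is unaffected.

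**What to change.** Make the name, the formula and the construct agree before analysis. The documents do not show which sentence reflects the investigators' intent, so the choice is theirs.

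- **Option (a):** keep Sample Entropy, replace the formula with −ln(A/B) from template matching, compute it by script on the tracked marker series, and prespecify m, r and any filtering or detrending. m = 2 with r = 0.2 SD is one option, not a requirement.
- **Option (b):** keep the formula, rename the outcome spectral entropy, and remove both the Sample Entropy label and the claim about non-linear dynamics.

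The cost is one or two sentences and, for (a), a short script in place of the spreadsheet. The recordings are unchanged.
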